#### **2.3.4. Study design**

We will conduct a case-control study (main study design) nested in a retrospective cohort of original articles submitted to leading medical journals of various specialties during an eight-year period (January 2012 through December 2019). The cases will be a randomly selected sample of original research articles sent for peer review. Due to low acceptance rates in some of the selected journals, we will conduct a stratified case-control study on the journal.

#### **2.3.5. Study population and eligibility criteria**

##### **2.3.5.1. Retrospective cohort study**

The study population is all articles submitted for publication in a list of invited medical journals in various medical specialties and with various impact factors or SCImago Journal Rank indicator, between 1 January 2012 and 31 December 2019 (Appendix 2). Medical journals publishing only non-human or basic-science research, case series or review articles will not be invited to participate.

##### **2.3.5.2. Case-control study**

The study population will be original research articles and systematic reviews submitted to participating journals that were externally peer reviewed and which focus on clinical and/or translational research. Original articles presenting results of non-human or basic-science research (animals, *in vitro*) will be excluded, as will non-research articles (clinical review articles, editorials, commentaries, protocols and letters). All articles where we are unable to identify the gender of the first author will be excluded.

#### **2.3.6. Selection of medical journals**

As the number of medical journals is constantly increasing, we needed to select journals on valuable indicators. Traditionally, journal-based metrics such as Journal Impact Factor (JIF, see glossary) were used to compare scientific output of individuals and institutions. However, this tool has several limitations, among them field specificity and lack of generalizability, and can be subject to manipulations by editorial policy. Indeed, the use of JIF is no longer recommended (San Francisco Declaration on Research Assessment [DORA]). We thus selected leading journals based on the SCImago Journal Rank indicator (see glossary), inviting those journals ranked in the first and second quartile to participate. We also invited journals based on opportunities. Currently, 27 of the 41 invited journals have agreed to participate (see Appendix 3-6, letters of support), and 11 declined (see Appendix 2). Among the 27 journals who agreed to participate, four journals provided limited access to their databases which did not allow us to apply our definitions and selection for cases and controls so we have had to exclude them. Finally, we only selected journals with a periodicity of publication of at least every two months and journals that receive over 100 research article submissions a year (Appendix 2). The application of these eligibility criteria left 23 journals willing to participate and share data.

### 2.3.7. Outcome measures and data collection

#### 2.3.7.1. Outcomes

In the case-control study, cases (primary outcome) will be **articles accepted for publication after peer review** and controls will be **articles rejected for publication after peer review**.

In the retrospective cohort study, **the acceptance rate of all submitted articles** by gender of first, last and corresponding author (secondary outcomes), will be determined. All original research articles and systematic reviews will be included. Additionally, we will record the rates of “reject without peer review”, revision requests, and later rejection throughout the manuscript’s cycle.

#### 2.3.7.2. Exposure variables and other confounders

The main exposure factor of interest is **first-author gender**. Other exposure factors assessed are: corresponding and last-author gender, handling-editor gender.

We will also collect data on: year of submission, study design, sample size, statistical significance of main results, funding disclosure, first author’s country of affiliation (reflecting somehow the author’s ethnicity/race), number of authors on the byline, number of reviewers who peer reviewed the manuscript, number (proportion) of women among all reviewers, number (proportion) of reviewers with same region of affiliation as the first author, and first author’s degrees (MD, PhD). If available, we will extract the reasons for rejection mentioned in the journal decision letter.

### 2.3.8. Random selection of original articles in case-control study

Random selection of original articles will be stratified by journal. Once journals agree to participate, we will ask for a list of all manuscripts (identified by their journal tracking number) submitted between 1 January 2012 and 31 December 2019. We will request additional information on whether the articles were peer reviewed and the final editorial decision: “accepted for publication” or “rejected”. We will randomly order the list of accepted and rejected manuscripts after peer review. In total, we calculated that among the 23 participating journals, depending on the first journal edition, we will have a total of 172 journal-years (BMJ Global Health and BMJ Paediatrics Open started respectively in January 1, 2016 and January 1, 2017). Thus based on our sample size estimation (see section 2.3.9.1) we will include 20 cases and 20 journals per journal-year, corresponding to a maximum of 160 cases and 160 controls per journal. In a second step, PDFs of all selected articles will be retrieved to extract additional data on study attributes.

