### **2.3.9. Statistical methods**

#### **2.3.9.1. Sample size**

As described above, we will consider an odds ratio of 0.85 for the acceptance for publication by first-author gender (0.85 for women versus men), to indicate the presence of gender bias. We assume a proportion of women first authors of 40% among cases and 44% among controls using  $OR=0.85$ . Taking into account a type-1 error at 5% (two-sided) with a study power of 90% and a correlation coefficient for exposure between matched controls and cases at 0.03 (to take into account some clustering at the journal level), this would require 2800 articles accepted and 2800 articles rejected after peer review. To take into account at least 20% of missing values among modelled variables, we will select a total of 3500 accepted and 3500 rejected manuscripts. We will randomly select an

equal number of articles per journal-year (20 cases and 20 controls) corresponding to a maximum of 160 cases and 160 controls for each journal. Currently, 23 journals have agreed to participate.

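### Section 2.3.8 counts 172 journal-years, but its own journals and dates give 175; at 20 per journal-year, 172 yields 3440 per group, not the stated 3500

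*Protocol*

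**What the plan says.** Section 2.3.6 ends its account of journal selection with "The application of these eligibility criteria left 23 journals willing to participate and share data". Section 2.3.8 asks each of these journals for manuscripts "submitted between 1 January 2012 and 31 December 2019" and then counts the sampling units: "In total, we calculated that among the 23 participating journals, depending on the first journal edition", "we will have a total of 172 journal-years". In brackets it gives a reason why the total is below eight years for every journal: "BMJ Global Health and BMJ Paediatrics Open started respectively in January 1, 2016 and January 1, 2017".

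Section 2.3.9.1 requires 2800 accepted and 2800 rejected articles for analysis. It inflates these for 20% missing values: "we will select a total of 3500 accepted and 3500 rejected manuscripts". The draw is to be an "equal number of articles per journal-year (20 cases and 20 controls"), with at most 160 of each per journal.

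**The concern.** The number of journal-years links the required sample size to the quota of 20. It is a plain count, so it should follow exactly from the number of journals, the window and the start dates. It does not.

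A reader who rebuilds the sampling frame from section 2.3.8 arrives at 3440 manuscripts per group. A reader who starts from section 2.3.9.1 arrives at 3500. At stake is whether the sampling scheme as written delivers the sample size that the same protocol says it needs, and whether an outsider can tell which journals contribute which years.

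**Working it through.** **Inputs from the protocol**

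- Journals: 23 (sections 2.3.6, 2.3.8 and 2.3.9.1).
- Window: 1 January 2012 to 31 December 2019, which is 8 calendar years (section 2.3.8).
- Late starters named: one on 1 January 2016, contributing 2016 to 2019 (4 years, 4 lost); one on 1 January 2017, contributing 2017 to 2019 (3 years, 5 lost) (section 2.3.8).
- Quota: 20 cases and 20 controls per journal-year (section 2.3.9.1). Section 2.3.8 has the word journals where controls is evidently meant.
- Required for analysis: 2800 per group. Missing-value allowance: 20%. Selection target: 3500 per group (section 2.3.9.1).

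**Step 1. The plan's selection target.** 2800 / (1 − 0.20) = 3500. This reproduces.

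**Step 2. The plan's journal-years.** 23 × 8 − 4 − 5 = 184 − 9 = 175, or equivalently 21 × 8 + 4 + 3 = 175. The stated 172 does not reproduce. Other readings:

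- No late starts: 23 × 8 = 184.
- Start year of each late journal not counted: 184 − 5 − 6 = 173.
- 22 journals, the number marked as selected in the rows of Appendix 2 that can be read here: 22 × 8 − 9 = 167. The table may be incomplete in this copy, so I use the stated 23.

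None of these gives 172. The sum 21 × 8 + 4 = 172 would arise if the second late starter were left out, but that is a guess at the cause. For 172 to be a true count of 23 journals, 184 − 172 = 12 journal-years must be missing, three more than the 9 explained by the two named journals.

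**Step 3. Manuscripts per group.**

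| Journal-years | Selected (× 20) | Evaluable (× 0.80) | Against 3500 / 2800 |
|---|---|---|---|
| 172 | 3440 | 2752 | −60 / −48 |
| 175 | 3500 | 2800 | 0 / 0 |

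The relative shortfall is 60 / 3500 = 1.7%. Reaching 3500 from 172 journal-years would take 3500 / 172 = 20.35 per journal-year, so a quota of 20 cannot do it.

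**Step 4. What the shortfall would cost.** I used the simple two-proportion normal approximation with the plan's 40% and 44%, two-sided 5%:

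power = Φ{ [0.04 × √n − 1.96 × √(2 × 0.42 × 0.58)] / √(0.40 × 0.60 + 0.44 × 0.56) }

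- n = 2752: (2.098 − 1.368) / 0.697 = 1.047, power 85.2%.
- n = 2800: (2.117 − 1.368) / 0.697 = 1.073, power 85.8%.

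The difference is about 0.6 percentage points. This formula ignores the plan's correlation of 0.03 and does not reproduce the stated 90%. That is a separate question; the formula is used here only to size the difference.

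**The case against.** The best defence is that the shortfall and the correction to 175 cannot both be right. If 172 is a slip for 175, the plan yields exactly 3500 and no article is lost. If 172 is the true count, writing 175 would put a false number into the protocol. This stands. Section 2.3.8 says that the count depends on each journal's first edition, and it names two journals without saying that they are the only exceptions. The figure of 175 assumes that the other 21 supply eight full years each. The fit of 175 × 20 with 3500 favours a slip but does not prove one. The objection limits what the correction may say; it does not remove the contradiction, because under either reading one printed figure must change.

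A second defence is size. With 3440 selected, 2800 evaluable articles are still reached if no more than 1 − 2800 / 3440 = 18.6% are lost, against a round allowance of 20%. That stands too.

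A reader might go further and infer that the target has no slack even at 175: the entry rule asks only for "journals that receive over 100 research article submissions a year", and section 2.3.4 speaks of low acceptance rates in some journals, so some journal-years may not hold 20 accepted articles. The documents do not support a figure for this. They give no acceptance rates for the selected journals as a set. The only rates reported, 45% and 27% by first-author gender in one journal (section 2.2), would give at least 27 accepted articles from 100 submissions. The plan also calls 160 per journal a maximum.

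Nor can articles with undetermined first-author gender be counted as a further loss. First-author gender is itself a modelled variable, so these articles may already fall within the 20% allowance.

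**Conclusion.** The inconsistency is real. On the protocol's stated inputs the count is 175 journal-years, and the stated 172 is incompatible with 3500 per group at 20 per journal-year. This rests on 23 journals, eight calendar years, and the two named journals being the only late starters. Only the last of these is in doubt, and if it fails, it is the 3500 that is not delivered.

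The size is small: at most 60 selected and 48 evaluable articles per group, 1.7% of the sample, and about 0.6 points of power. A reader might conclude that the study is materially underpowered because of the miscount; these numbers do not support that. It is a consistency error in the sampling frame, and it does not threaten validity. It is still worth correcting, because the two sections give two totals for the same draw.

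**What to change.** Recount the journal-years from the final journal list and each journal's first year of submissions, and show the sum in section 2.3.8.

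- If only the two named journals started late, change 172 to 175 and add 175 × 20 = 3500, in agreement with section 2.3.9.1.
- If 172 is right because other journals have fewer than eight years, name them with their start dates. Then restate the selection target in section 2.3.9.1 as 3440 per group, about 2752 evaluable, with the power that this gives under the plan's own method.

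In the same edit, correct the word journals to controls in the quota sentence of section 2.3.8. The cost is a check of the journal list and one or two sentences. The quota of 20, the maximum of 160 per journal and the mixed-effects model with journal as random effect can all stay as they are. Refilling short journal-years from other journals is not needed for this point. It would conflict with the equal number per journal-year, and with the 160 maximum for any donor journal that already has its full quota.

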#### 2.3.8.1. Data extraction

##### 2.3.8.1.1. Extraction for the case-control study

We will complete data extraction (study design, statistical significance of main result, etc.) from the manuscripts by using text mining techniques. For this specific task, we will collaborate with the Swiss Institute of Bioinformatics (SIB), Bibliomics and Text Mining Group (BiTeM, [name]) through a study partnership. All prespecified variables will be automatically extracted using an algorithm created by our project partner at the SIB and recorded in a database. Data on manuscripts, authors, editors and reviewers involved will be obtained directly from the journals and merged with the dataset (list of variables; see appendix 7).

#### **2.3.8.1.2. Extraction for the retrospective cohort study**

Regarding variables for the retrospective cohort, most variables will be directly exported from the journal systems in plain text (CSV or XLS). These variables will include the date of submission, the article's first decision and last decision, the authors' the countries of affiliation, and the journal identifier (case report form; see appendix 8). We will complete data extraction (for study design, statistical significance of main result, etc.) from the abstracts of the manuscripts by using text mining techniques elaborated by our project partner.

#### **2.3.8.1.3. Identification of authors' gender**

The identification of first, corresponding and last author's gender will be performed independently of the editorial decision (accepted or rejected for publication) via an internet search using specific tools by a collaborator in the research team. This will be performed separately for the case-control study and for the retrospective cohort study. Determination of authors' gender will be based on first name, middle name, salutation and the country of the author's affiliation. We will use binary gender identification that will not be based on the self-reported gender identity. We will determine gender by using a sequential four step procedure. Firstly, we will use both first name and country to search in the Gender API (<https://gender-api.com/en>) website. Gender API provides gender determination with an accuracy probability from 50% to 100% (under 50% an unknown status is attributed), gives the number of samples retrieved to search for the information, ensures that the level of misclassification is around 5%, and has the highest coverage on the variability in name origins. We will set gender accuracy above 60% as the minimum criterion for inclusion in the primary gender determination. Secondly, for all authors with undetermined or unknown gender based on the above, we will use the authors' given middle names and country to search in Gender API. Thirdly, we will use the online service genderize.io (<http://genderize.io>) to determine gender on the basis of first names and middle names, also using an accuracy above 80% as the minimum criterion. Fourthly, for still undetermined gender, we will use the authors' title/salutation and attribute it male gender to "Mr" or "M" and female gender to "Miss," "Mrs," and "Ms." Where none of these methods determine the gender, we will record the gender as undetermined.

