#### **2.3.8.1.4. Final dataset for case-control study**

We will disaggregate the editorial decision variables from the submission data so that determination of author's gender and all other data extraction will be done blinded to editorial decision. Finally, for analysis we will combine the separate databases using the manuscript identity number.

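### A name-based gender call just above 60% accuracy is final and is never checked against a recorded gendered salutation, which leaves some avoidable misclassification in the main exposure

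*Protocol*

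**What the plan says.** Protocol section 2.3.8.1.3 fixes both the order of the steps and the cut-offs.

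- **Step 1** (Gender API, first name and country): "We will set gender accuracy above 60% as the minimum criterion for inclusion in the primary gender determination".
- **Step 2** is reached only by those left over: "Secondly, for all authors with undetermined or unknown gender based on the above, we will use the authors' given middle names and country".
- **Step 3** (genderize.io, first and middle names, country not mentioned): "also using an accuracy above 80% as the minimum criterion".
- **Step 4** is the salutation, again only for those left over: "Fourthly, for still undetermined gender, we will use the authors' title/salutation". Mr and M count as male; Miss, Mrs and Ms count as female.

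The same section says of Gender API that it "ensures that the level of misclassification is around 5" per cent, without tying that figure to any cut-off. Section 2.3.8.1.4 adds that "determination of author's gender and all other data extraction will be done blinded to editorial decision". Section 2.3.5.2 states the consequence of failing all four steps: "All articles where we are unable to identify the gender of the first author will be excluded".

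**The concern.** The protocol accepts the salutation as evidence of gender, since step 4 relies on it alone when names fail. Yet a salutation on file cannot overrule, or even be compared with, a name call only slightly better than a coin toss. If the Gender API score is read as the probability of being right, names scoring 60-80% carry an expected error of 20-40%. Part of that error could be removed with data the study intends to use anyway.

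First-author gender is the main exposure (section 2.3.7.2). Error in a binary exposure that does not depend on the outcome pulls the odds ratio toward 1 and costs power. Section 2.3.9.1 treats an odds ratio of 0.85 as indicating bias, and section 1.4 draws a substantive conclusion if none is found, namely that the imbalance more likely arises upstream of editorial decisions. Attenuation favours that conclusion. The sample size carries no allowance for it: its 20% is for missing values.

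**Working it through.** **Inputs from section 2.3.9.1:** women first authors 40% of cases and 44% of controls; two-sided 5%; power 90%; exposure correlation 0.03; 2800 per group. **From section 2.3.8.1.3:** misclassification about 5%. **Assumed, because the documents do not give them:** the share s of first authors scoring 60-80% (2%, 5% or 10%); 30% error in that band (midpoint of 20-40%); and the fraction r of the band's errors that a salutation corrects.

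**1. The plan's own figure.** n = [1.96·√(2·p̄·(1−p̄)) + 1.2816·√(p1(1−p1) + p0(1−p0))]² / (p0−p1)², with p1 = 0.40, p0 = 0.44 and p̄ = 0.42:
(1.3680 + 0.8938)² / 0.0016 ≈ 3198 per group.
The matched case-control formula with correlation 0.03 gives 3367. The stated 2800 is not reproduced; it yields 85.8% power by the first formula and about 84% by the second. That gap is a separate matter. It is noted here only because the no-error baseline below is 85.8%, not 90%.

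**2. Effect of total misclassification.** With symmetric error e, the same in cases and controls, the observed share is p(1−e) + (1−p)e, that is 0.40 + 0.20e in cases and 0.44 + 0.12e in controls. At e = 0.05 these are 0.410 and 0.446, and the odds ratio is (0.410/0.590)/(0.446/0.554) = 0.863.

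| Total error | Odds ratio | Power at 2800 per group |
|---|---|---|
| 0% | 0.848 | 85.8% |
| 3% | 0.857 | 81.2% |
| 5% | 0.863 | 77.7% |
| 10% | 0.878 | 67.5% |

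Unequal errors also move the odds ratio toward 1: sensitivity 0.95 with specificity 1 gives 0.853, and 0.97 with 0.90 gives 0.869.

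**3. The part a salutation check could remove.** Take total error as 5%, including the band. After correction, e = 0.05 − s × 0.30 × r.

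| Share in 60-80% band (s) | Errors corrected (r) | Remaining error | Odds ratio | Power |
|---|---|---|---|---|
| 2% | half | 4.70% | 0.862 | 78.3% |
| 2% | all | 4.40% | 0.861 | 78.8% |
| 5% | half | 4.25% | 0.861 | 79.1% |
| 5% | all | 3.50% | 0.859 | 80.4% |
| 10% | half | 3.50% | 0.859 | 80.4% |
| 10% | all | 2.00% | 0.854 | 82.9% |

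If only a quarter were corrected, the odds ratio would be 0.863 (s = 2%) to 0.861 (s = 10%), and power 78.0% to 79.1%.

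**The case against.** **Total error is not the effect of the 60% rule.** A reader might infer from the first table that the rule costs about 8 points of power (85.8% to 77.7%), or more at 10% error. The documents do not support that. The 5% is the protocol's figure for Gender API overall, and 10% has no source in it. Only the increment in the second table is relevant. This objection stands.

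**The 60% and 80% cut-offs need not conflict.** It is tempting to call them contradictory. They belong to different tools with different inputs, and tool-specific thresholds are legitimate. What remains is wording: the *also* before the 80% suggests that the same threshold applied before, when the only one stated is 60%.

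**The 80% tool is not shown to be better.** Genderize.io is described without country, whereas the step 1 score uses it. Nothing shows that 80% without country beats 60-80% with country, so letting genderize.io override, or imposing 80% throughout, is not supported. A higher step 1 cut-off alone could also push more articles into exclusion.

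**Blinding does not by itself make the error non-differential.** It removes error driven by knowledge of the decision. Name ambiguity may still vary with country, and the protocol itself suspects geographical bias in acceptance. Attenuation is therefore a conditional claim, best made given country, which is collected.

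**Name before salutation may be deliberate.** The study concerns decisions by editors and reviewers, section 2.5.1 discusses assumptions made from first names, and gender is not taken from self-report. That is a fair argument for starting with the name. It is weaker for leaving an ambiguous name uncorrected when the protocol accepts the salutation as sufficient in step 4.

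**Salutations may seldom help.** Titles such as Dr or Prof are uninformative, and many first authors hold an MD or PhD. How often a usable title exists is not stated, so the lower rows of correction may be the realistic ones.

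**Conclusion.** The point holds in a limited form. The protocol states, rather than leaves open, that a Gender API result just above 60% is final and that a contradicting gendered salutation is ignored. Some misclassification of the main exposure is therefore avoidable. If the error is unrelated to acceptance given country, it biases the primary odds ratio toward 1.

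Under the assumptions shown, correcting half to all of the band's errors shifts the odds ratio by about 0.001 to 0.009 and raises power by about 0.6 to 5.2 points. The true figure depends on the share of authors in the band and on how often a gendered title is recorded, neither of which is in the documents. The calculation uses crude proportions and symmetric error, not the adjusted mixed-effects model. Most of the attenuation from 5% total error would remain after the change, and the shortfall from 90% power with no error at all is unrelated. The case for acting rests on the very low cost, not on a large effect.

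**What to change.** 1. For Gender API results of 60-80%, let a recorded Mr, M, Miss, Mrs or Ms decide. Where there is none, keep the Gender API result, so that no article is lost to the exclusion in section 2.3.5.2.
2. Do not let genderize.io, as described without country, automatically override a country-specific Gender API score.
3. Run the primary model once more, restricted to assignments made by salutation or at 80% accuracy or above. This is a recommended addition that could sit in the SAP; its absence from the protocol is not counted as an error.
4. Correct the *also* in step 3 so that each tool's threshold is unambiguous.

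The cost is a little extra data handling and one extra model run. Coverage is unchanged. Authors recorded as Dr or Prof gain nothing from the change.
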